### 8.2 Secondary study parameters

Dichotomous secondary outcomes will be analysed using the same method as the primary outcome. Continuous data of secondary outcomes will be assessed using a linear mixed model to estimate mean differences, with random intercepts and slopes as appropriate. Median differences will be calculated as appropriate.

#### 8.2.1 Quality of life

To get an impression of the impact of (suspected) early-onset sepsis on the quality of life (QoL) of both parents/guardians and their child, parents/guardians will be asked to fill in a questionnaire on day 14. See also 6.1.2. Outcome reporting will be mainly descriptive. Mixed models can be used to further explore the effect of treatment and center if a trend is observed for some of the questions. Mean scores and standard deviations are calculated for composite indicators. We use t-tests to evaluate differences in mean scores between groups for normally distributed data. The significance level is set at an alpha value of  $<.05$ .

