## 2. OBJECTIVES

The primary objectives of this study are:

1. To investigate whether the use of the EOS calculator safely reduces antibiotic exposure in newborns with suspected EOS in the first 24 hours after birth.
2. To investigate the presence of one or more of the following four predefined safety criteria, namely 1) the need for any respiratory support, and/or 2) the need for an intravascular fluid bolus for hemodynamic instability due to sepsis, and/or 3) referral to a Neonatal Intensive Care Unit for sepsis treatment, and/or 4) proven EOS.

Secondary objectives of the study are:

1. To investigate if the use of the EOS calculator decreases the total duration of antibiotic therapy in newborns with suspected EOS.
2. To investigate if the use of the EOS calculator decreases the percentage of antibiotic therapy started for suspected and, or proven EOS if symptoms started between 24-72 hours after birth.
3. To study the impact of (suspected) EOS on parents/guardians.

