#### 6.1.2 Secondary study parameters/endpoints

- The total duration of antibiotic therapy.
- The proportion of antibiotic therapy started for suspected and, or proven EOS if symptoms started between 24-72 hours after birth.

- Quality of life: To get an impression of the impact of (suspected) early-onset sepsis on the quality of life (QoL) of both parents/guardians and their child, parents/guardians will be asked to fill in a questionnaire on day 14 after birth. Our questionnaire is based on (parts of) two questionnaires, which were used in different studies assessing the effect of early intravenous-to-oral antibiotic switch (30), and the influence of resiliency and stress on parental/guardian perspective of the future QoL of their newborns (31). The first part collects information on medical factors after hospitalization (side effects, number of medical visits, readmission, and medication use) and basic needs of the newborn (sleep quality of the patient, (breast)feeding success rate). The second part addresses the subjective parental/guardian evaluation of the impact of newborns' admission, and parental/guardian projection of future QoL of their newborn. The last part of the questionnaire collects demographic data. We hypothesize that the maternity period is experienced more positive if mother and child go home quickly, because of less hinder to take care of their child (for example, earlier initiation of breastfeeding), and less stress (for example, emotionally or financially). The questionnaire is designed in close collaboration with Care4Neo. Care4Neo (formerly Association of Parents of Incubator Children) represents the interests of parents/guardians whose child is admitted to a hospital immediately after birth.

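### Section 8.2.1 lets quality-of-life questions be modelled only after an undefined trend is seen, and sets a .05 level for reporting it describes as largely descriptive (minor)

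*Protocol*

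**What the plan says.** Protocol section 8.2.1 gives four statements on the questionnaire.

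- On status: "Outcome reporting will be mainly descriptive".
- On the scores: "Mean scores and standard deviations are calculated for composite indicators". Neither their number nor their names are given.
- On testing: "We use t-tests to evaluate differences in mean scores between groups for normally distributed data", followed by "The significance level is set at an alpha value of" less than .05.
- On modelling: "Mixed models can be used to further explore the effect of treatment and center if a trend is observed for some of the questions". What counts as a trend, and who judges it, is not stated.

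Section 6.3 puts the questionnaire at 22 to 32 questions; section 6.1.2 shows that some of these are demographic. Section 8.2 names a linear mixed model for continuous secondary outcomes. Section 8.1 rests the conclusion on effectiveness on the two co-primary outcomes, both of which must be met.

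**The concern.** Two things in section 8.2.1 do not fit together well.

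First, descriptive reporting needs no significance level. Once a .05 level is written down for t-tests, a p-value below it will be read as a finding, whatever the preceding sentence says about status.

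Second, the modelling rule depends on the data. A treatment effect is modelled for a question because that question already shows a difference, and the model is fitted to the same answers. Questions without a visible difference get no model. The set of modelled effects is then tilted towards chance differences, and a reader who sees only that set cannot tell how many questions were passed over.

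At stake is how quality-of-life results are read, in a trial whose results are meant to feed into guidelines (section 10.6). The main conclusion is not at stake.

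**Working it through.** The protocol gives no error rate for the quality-of-life analyses beyond the .05 level, so there is no figure of its own to reproduce.

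**1. Effect of the trigger on the questions chosen.** Assumptions: no true difference on the question; a trend means a two-sided p below a threshold t; the same test serves for screening and for the model. The protocol fixes none of these. A null p-value is uniform, so for t of at least .05:

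share significant among chosen null questions = P(p<.05) / P(p<t) = .05 / t

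- t = .20: .05/.20 = 25%
- t = .10: .05/.10 = 50%

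**2. Effect on the estimates.** Under the same assumptions, the mean absolute difference of a null question is √(2/π) = 0.80 standard errors. Among chosen questions it is 2φ(z)/t, where φ is the normal density and z the two-sided cut-off for t:

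- t = .20, z = 1.282: 2 × 0.1755/.20 = about 1.8 standard errors
- t = .10, z = 1.645: 2 × 0.1031/.10 = about 2.1 standard errors

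So the modelled effects look at least twice as large as chance alone gives across all questions.

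**3. What the trigger does not do.** Out of 100 null questions, 20 would be chosen at t = .20, and 5 of those would be significant. Without any screening, 5 of the 100 would be significant as well. Screening removes questions; it adds no significant ones. The unconditional error per question stays at 5%.

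**4. Family-wise rate.** For k independent null tests at two-sided .05, the chance of at least one false positive is 1 − .95^k in either direction, and 1 − .975^k in the direction of benefit.

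| k (assumed) | Either direction | Benefit only |
|---|---|---|
| 1 | 5.0% | 2.5% |
| 3 | 14.3% | 7.3% |
| 5 | 22.6% | 11.9% |
| 10 | 40.1% | 22.4% |

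Positive correlation between scores lowers the figures for k above 1. Because k is not stated, the table shows only how wide the range is. The count of 22 to 32 questions cannot stand in for k: it includes demographic items, and the t-tests are planned for composite scores, not for single questions.

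**The case against.** The strongest defence is that nothing confirmatory depends on this text. Section 8.2.1 states its aim as gaining an impression, presents the models as optional further exploration, and attaches the .05 level to the t-tests rather than to the models. The third secondary objective in section 2 is not directional. The expectation in section 6.1.2, "We hypothesize that the maternity period is experienced more positive if mother and child go home quickly", concerns early discharge and is not a direct comparison of the two arms. All of this stands, and it is why the point is minor. It does not remove the trigger, however. A statistical analysis plan could define a trend, but choosing questions on that definition would still be selective.

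A reader might go further in two ways that the protocol does not support.

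- One might infer that a false quality-of-life benefit is several times more likely than 5%. That needs a number of tests that the protocol does not give, and it must not count false harms as benefits. In the benefit direction, three independent tests give 7.3%.
- One might extend the criticism to the two clinical secondary outcomes, because section 2 words the first as "To investigate if the use of the EOS calculator decreases the total duration of antibiotic therapy in newborns with suspected EOS" and section 8.2 says "Dichotomous secondary outcomes will be analysed using the same method as the primary outcome" without a testing order. Two independent tests carry a false-benefit chance of 1 − .975² = 4.9%. Handling of multiplicity among secondary outcomes is commonly left to the statistical analysis plan, which is not at hand, so its absence from the protocol is not an error.

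**Conclusion.** The point holds for the wording of section 8.2.1 only, and it is minor. The section combines largely descriptive reporting with a .05 level on an unstated number of scores, and it lets an undefined trend decide which questions receive a treatment-effect model. Estimates and p-values from those models would be selective: 25% or 50% of chosen null questions would be nominally significant, given the assumed thresholds of .20 or .10 and the same test at both steps. The error per null question over all questions remains 5%, no family-wise rate can be derived from the protocol, and the conclusion on effectiveness is not affected.

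**What to change.** Change section 8.2.1 only:

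- Delete the condition that a trend must be observed before a model is fitted.
- Delete the .05 significance level.
- Analyse every quality-of-life score with one pre-set model, whatever the data show: the linear mixed model that section 8.2 already names for continuous secondary outcomes.
- Report all estimates with 95% confidence intervals, labelled exploratory.

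Using the section 8.2 model in place of the t-test also takes account of hospital, which the t-test does not. As an illustration, suppose that the intracluster correlation of 0.0025 in section 4.4 applied to a score (an assumption) and that all 183 newborns per hospital had a questionnaire. The design effect would be 1 + 182 × 0.0025 = 1.455. The effective cut-off would fall to 1.96/√1.455 = 1.625, and a nominal 5% t-test would reject about 10.4% of the time under no effect.

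The change needs no extra patients, data or visits. Its cost is that the sponsor can no longer call a quality-of-life difference statistically significant.

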### 3. STUDY DESIGN

**Design:** We will conduct a prospective, cluster-randomized trial. We aim to include 1830 newborns from 10 hospitals in the Netherlands during an 18-month period. Cluster-randomization happens at the hospital level. A cluster is finished when a total of 183 participants are included into the cluster. Once finished, a hospital cannot be randomized again. Participating hospitals provide care up to Level II special care for stable or moderately ill newborns, with annual birth rates between 1200 and 4000 births per year, and all use the Dutch national guidelines to guide antibiotic use in newborns at-risk for EOS.

This cluster randomized design can be used when randomization at individual level is difficult and/or creates possibility for bias. The cluster-randomized study design matches our study objectives perfectly because time for randomization is very restricted due to the immediate need to start antibiotic therapy in some newborns. Furthermore, the clustered approach prevents confusion and contamination between the different protocols being compared, thereby limiting bias. After randomization, the assigned protocol is considered standard care for newborns with suspected EOS within 0-24 hours after birth during the study period in that hospital. This means that the NVK guidelines or the EOS calculator (depending on randomization) will be used for all newborns at risk for EOS (within 0-24 hours after birth) in the particular hospital, independent of study participation. It is noteworthy that every attending physician always has the option to choose for clinical management according to another protocol instead of the assigned protocol.

Newborns who do not meet the inclusion criteria, and develop clinical symptoms (suspected for EOS) >24 hours after birth, the NVK guidelines will be used since the EOS calculator is only validated for use in the first 24 hours after birth. If newborns are eligible for inclusion and attending physicians opt for clinical management not according to the advice of the assigned study protocol, this will be recorded with deviations being noted with accompanying justification in both the electronic health record and the electronic Case Report Form (eCRF). After informed consent is obtained data will be collected and used for analysis, and follow-up data collection will ensue.

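### Section 8.2.1 compares quality-of-life scores with t-tests that ignore hospital clustering, so the false-positive rate exceeds the nominal 5% at any positive ICC

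*Protocol*

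**What the plan says.** Protocol section 3 fixes the unit of allocation: "Cluster-randomization happens at the hospital level". Section 4.1 gives ten centres, five per arm.

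Section 6.1.2 lists quality of life, from a parent questionnaire on day 14, among the secondary endpoints. For that class of outcome section 8.2 states: "Continuous data of secondary outcomes will be assessed using a linear mixed model to estimate mean differences, with random intercepts and slopes as appropriate".

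Section 8.2.1, the subsection on this endpoint, says four things:

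- On status: "Outcome reporting will be mainly descriptive".
- On mixed models: "Mixed models can be used to further explore the effect of treatment and center if a trend is observed for some of the questions".
- On the comparison itself: "We use t-tests to evaluate differences in mean scores between groups for normally distributed data".
- On the threshold: "The significance level is set at an alpha value of" less than .05.

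Nothing in section 8.2.1 ties the t-test to hospital, whether through a random effect, a variance correction or analysis of hospital means.

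**The concern.** An ordinary two-sample t-test takes every family as an independent observation. Here all families in a hospital share one allocation, and whatever they have in common through that hospital stays inside the arm difference. With five hospitals per arm it does not average out as the t-test assumes. The test's standard error leaves this component out.

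The protocol accepts the principle elsewhere. Section 4.4 puts an ICC into both sample-size calculations, and sections 8.1 and 8.2 use models with random effects per cluster. The questionnaire comparison is the exception.

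The optional mixed model does not repair this. It is triggered by an observed trend, and a trend judged without regard to hospital is what clustering makes too easy to find. It is also described as further exploration, so the t-test remains the stated comparison.

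At stake is how a positive questionnaire result is read: a difference between two sets of five hospitals may be reported as an effect of the calculator on families.

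**Working it through.** **Inputs.** From section 4.4: ICC 0.0025 (given for the two binary co-primary outcomes only), 164 per hospital before drop-out, 10% drop-out, 183 per hospital planned. From sections 3 and 4.1: ten hospitals, five per arm. From section 8.2.1: alpha .05, taken as two-sided because the sidedness is not stated. Assumed, because the protocol gives neither: questionnaire ICCs from 0.001 to 0.01, and response from 50% to 100%.

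**The plan's own figures first.** Cluster size: 164/0.9 = 182.2, rounded up to 183; 10 × 183 = 1830, as stated. Use of the ICC: 40% against 25% at two-sided 5% and 80% power needs 152 per arm under individual randomisation. With design effect DE = 1 + (m − 1) × ICC and five hospitals per arm, this becomes 152 × (1 − 0.0025)/(1 − 152 × 0.0025/5) = 151.62/0.924 = 164.1 per arm. That is 328 in total, or 330 in whole hospitals of 33. The stated 330 is reproduced, so the design effect below is the one that reproduces the protocol's own calculation.

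**Error of a t-test that ignores hospital.** The true standard error is √DE times the one used, so

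true alpha = 2 × [1 − Φ(1.96/√DE)].

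At ICC 0.0025:

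- m = 183: DE = 1 + 182 × 0.0025 = 1.455; 1.96/1.206 = 1.625; true alpha 10.4%.
- m = 164: DE = 1.4075; true alpha 9.9%.
- m = 128 (70% response): DE = 1.3175; true alpha 8.8%.
- m = 100: DE = 1.2475; true alpha 7.9%.
- m = 92 (50% response): DE = 1.2275; true alpha 7.7%.

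A simulation of ten normal clusters, 40,000 runs per setting, agrees: 10.3% at m = 183, 10.0% at 164, 8.9% at 128 and 7.9% at 92. With no clustering it returns 4.9% at m = 183.

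**Range over the unknown ICC (true error of a nominal 5% test, by the formula).**

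| Responders per hospital | ICC 0.001 | ICC 0.0025 | ICC 0.005 | ICC 0.01 |
|---|---|---|---|---|
| 183 | 7.1% | 10.4% | 15.6% | 24.3% |
| 164 | 6.9% | 9.9% | 14.6% | 22.7% |
| 128 | 6.5% | 8.8% | 12.5% | 19.3% |
| 92 | 6.1% | 7.7% | 10.4% | 15.6% |

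**When the error reaches 10%.** This needs DE ≥ (1.960/1.645)² = 1.42. At ICC 0.0025 that means m ≥ 1 + 0.42/0.0025 = 169 responders per hospital, or 169/183 = 92% return. At 92 responders it needs an ICC of at least 0.0046.

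**The case against.** Five arguments can be made for the plan.

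*The endpoint is mainly descriptive.* True, and it limits the consequence. But the same paragraph names a test and a significance level, and section 6.1.2 states a directional hypothesis about how families experience the maternity period. Where a test is run, it should be valid for the design.

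*Section 8.2.1 is a specific exception to section 8.2, so the text is not contradictory.* This is a fair reading. The point does not need a contradiction: an exception that drops the clustering is unsuitable for allocation by hospital, whether or not it was intended.

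*Groups is not defined.* If the groups varied within hospitals, for example treated against untreated newborns, the design effect used above would not apply. The trial arms are the more natural reading, because the sentence on mixed models speaks of treatment and center effects. The size given here rests on that reading.

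*The ICC is borrowed.* This stands. The figure of 0.0025 belongs to the binary co-primary outcomes. Applying it to questionnaire scores is an assumption, as is every other value in the table.

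*The statistical analysis plan may settle it.* It is not at hand. But the protocol does not leave the method open: a plan following section 8.2.1 would carry the fault forward, and one following section 8.2 would depart from section 8.2.1.

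A reader might infer from the 10% figure that the false-positive rate is at least doubled. The documents do not support that as a lower bound. With the borrowed ICC, doubling needs about 169 of 183 questionnaires returned per hospital. At 164 the error is just under double, and at 92 it is about 1.5 times nominal. A larger ICC would push it above double, but the protocol gives none for these scores.

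**Conclusion.** The point holds. As written, section 8.2.1 tests composite scores with a method that assumes independent families in a trial allocated by hospital, and the error exceeds 5% at any positive ICC. That direction needs no assumption beyond reading the groups as trial arms.

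The size does rest on assumptions. It is about 10% at the planned 183 per hospital with the borrowed ICC of 0.0025, about 8% with 92 to 100 responders, and about 6 to 24% across ICCs of 0.001 to 0.01 and 50 to 100% response.

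A reader might also infer that the trial's main conclusion is at risk. It is not: section 8.1 analyses both co-primary outcomes with a mixed model that carries cluster effects. The consequence is confined to a secondary, mainly descriptive endpoint, where a hospital difference may be taken for a calculator effect. The fault is worth correcting because it is clear and the correction is cheap.

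**What to change.** Replace both the t-test sentence and the conditional mixed-model sentence in section 8.2.1. The new text should say that any between-arm comparison of composite scores uses the linear mixed model of section 8.2, with a random intercept for hospital and a small-sample correction, and is not conditional on an observed trend. A t-test on the ten hospital means, with 10 − 2 = 8 degrees of freedom, is a simple alternative. The exact form of the correction can be left to the statistical analysis plan. If no between-arm testing is intended, the t-test and its alpha should be removed and the reporting kept descriptive. It would also help to state that groups means the trial arms.

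The change needs no further participants or data. The cost is wider confidence intervals. With the hospital-means test at m = 183 and ICC 0.0025, the standard error grows by √1.455 = 1.21 and the critical value moves from 1.96 to 2.306 (t, 8 df). The interval is then roughly 1.21 × 2.306/1.96 = 1.42 times as wide. The nominal 5% is restored with the hospital-means test, and approximately restored with the corrected mixed model.

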### 8.3 Interim analysis

There are two interim analyses planned, which are based on safety. However, efficacy may be associated with safety. Interim safety review will use descriptive statistics only. See 'K5. DSMB Charter' for more details.

## 9. ETHICAL CONSIDERATIONS

### 9.1 Regulation statement

The study will only start after written approval from the Independent Ethics Committee (IEC), which operates according to ICH GCP guidelines. The investigator is responsible for submission to and communication with the IEC.

The study will be conducted in accordance with the principles of the declaration of Helsinki (October 2008), the ICH GCP guidelines (CPMP/ICH/135/95), the Regulations on Medical Research involving Human subjects (Medical Research involving Human subjects Act, Wet Medisch Wetenschappelijk Onderzoek met mensen WHO, 1999), and the Medical Device Regulation (MDR/2017/745). The investigator will not implement any amendment of the protocol without IEC approval, except when changes involve only logistical or administrative aspects of the study.

### 9.2 Recruitment and consent

The study will be conducted according to the “Code of conduct relating to expressions of objection by minors participating in medical research” approved by the Board of the Dutch Association of Paediatric Medicine (NVK) on 21 May 2001, see Appendix I. Parents or guardians are free to decide to withdraw from the study at any stage, and for any reason, without prejudicing their child’s further treatment.

#### *Recruitment of patients*

Within the first 24 hours after birth parents or guardians of eligible newborns (whom are at risk for EOS) will be approached by local principal investigators or research nurses, which are well trained (according to ICH GCP) and highly engaged in the study. The parent(s)/guardian(s) will receive more extensive information (in Dutch or English) in the patient information and consent form. Prior to entering the study, the investigator will explain to the parent(s)/guardian(s) the nature of the study, its purpose, procedures, expected duration, and the benefits and risks involved in study participation.

The patient will be given sufficient time to read the patient information and the informed consent form and has the opportunity to ask questions before signing the informed consent form. The investigator or research nurse will answer all study-related questions. The right to withdraw from the study at any time without prejudice will be clearly communicated. After this explanation and before any study-specific procedures have been performed, the patient, as well as the investigator/research nurse, will voluntarily sign and date an informed consent form.

The policy (observation and/or antibiotic therapy) is not conducted by participating in the study, since the assigned protocol is considered standard care for newborns with suspected EOS during the study period. (See also chapter 3 and 6.2.) No additional painful procedures will be performed. These things will make it more likely parents/guardians will give permission to participate.

A newborn is at risk for EOS if at least one maternal risk factor or neonatal clinical sign is present (in accordance with the NVK guideline, listed in table 1). After determining eligibility, the advice of either the NVK guideline or the EOS calculator is followed (depending on randomization). The observation period will be at least 12 hours for the control group (NVK guideline) and 24 hours for the intervention group (EOS calculator), which consists of routine controls of vital parameters (heart rate, respiratory rate, and temperature) every 3 hours by the nurse, and a minimum of two physical examinations (within 4 hours after birth and before discharge) by the physician.

